#### Chronic Pain Acceptance

The Chronic Pain Acceptance Questionnaire (CPAQ-8) short form is an 8-item validated instrument that assesses one’s engagement in personally meaningful activities despite pain, as well as efforts directed at controlling pain (example item: “I am getting on with the business of living no matter what my level of pain is”) [52]. Respondents rate each item using a 6-point scale ranging from 0 (never true) to 5 (always true).

#### Device Utilization

The custom device utilization survey is a single-item instrument that assesses the number of VR sessions completed since the last time it was asked. Respondents select either (1) 0, (2) 1, (3) 2, (4) 3, or (5) 4 or more. This survey is administered on a biweekly basis.

#### System Usability Scale

The System Usability Scale is a validated, 10-item attitude Likert scale giving a global view of subjective assessments of usability (example item: “I thought the system was easy to use.”) [53]. Participants rate each item using a 5-point response scale ranging from "Strongly Disagree" to "Strongly Agree." Some items are reverse scored, a multiplier is applied to the sum total, and total SUS scores range from 0-100.

#### Immersive Tendencies Questionnaire

The Immersive Tendencies Questionnaire (ITQ) is a 29-item survey that measures difference in tendencies of individuals to experience presence [54]. The involvement subscale was chosen by the coauthors to reduce participant burden with just 7 items that focus on propensity to be engaged with content such as reading a book or watching a movie.

#### Assessment of Affect

The Positive and Negative Affect Schedule (PANAS) is a validated 20-item survey to assess the affect of each participant [55]. They will be asked to the extent they have felt specific emotions on a Likert scale from 1 “Very Slightly or Not at All” to 5 “Extremely.”

#### Prescription Opioid and Analgesic Medication Use

A custom survey was also created to assess analgesic medication use. The medication survey consists of 3 main questions to assess for the use of the following: prescription medication, over-the-counter medication, or other medications. Prescription opioid data will be converted to a standardized morphine milligram equivalent daily dose using the Centers for Medicare & Medicaid Services “Opioid Oral Morphine Milligram Equivalent (MME) Conversion Table” [56]. Endorsement of prescription medications will prompt additional items to collect the type of medication, frequency of use, dose, happiness with one’s current prescribed medication regimen, and interest in changing one’s current prescribed medication regimen.

#### Health Care Utilization

We will also assess cLBP health care utilization in terms of frequency of steroid injections, lower back surgery, emergency department visits, hospital admissions, and unplanned physician visits over various periods.

#### Additional Custom Surveys

Several custom surveys were developed for the study, including one designed to assess satisfaction with each condition. Another assesses device usability, enjoyment or difficulties, and the likelihood to continue treatment. Additional items will assess pain knowledge and pain management skills use (eg, use of relaxation and controlled breathing during the previous 7 days). We will also assess patient perception of the study arm using a single item administered to both groups in the 6-month follow-up survey.

**Table 1 table1:** Variable/category, measure name, rank, and number of items for all measures.

Variable or Category		Measure	Number of items or units
**Primary Outcome**			
	Pain intensity/Pain interference (activity, mood, sleep, stress)	DVPRS-I^a^ Pain Scale and DVPRS-II Pain Scale Measures [36]	5
**Secondary Outcomes**			
	Global impression of change	Patient’s Global Impression of Change (PGIC) [38]	1
	Physical function	PROMIS^b^ Physical Function [40]	6
	Sleep disturbance	PROMIS Sleep Disturbance [41]	6
	Acceptability	Custom Patient Satisfaction	8 + 15 open-ended questions
	Adherence	Custom Device Utilization survey	1
	Adherence	VR^c^ usage data	Seconds/week
	Pain self-efficacy	Pain Self-Efficacy Questionnaire (PSEQ) [51] (general) and Custom Pain Self-Efficacy Questionnaire with VR as a referent (inside the VR headset and outside the VR headset)	2 in each
	Pain acceptance	Chronic Pain Acceptance Questionnaire (CPAQ) [52]	8
	Pain catastrophizing	Pain Catastrophizing Scale (PCS^d^) [49]	4
	Pain medication	Custom Analgesic Medication Use Survey	3 with branching logic to additional 7
	Health care utilization	Custom health care utilization survey for cLBP^e^	5 at baseline and 6 at all other timepoints
	Other measures		
	Assessment of affect	Positive and Negative Affect Schedule (PANAS) [55]	20
	Susceptibility to virtual reality treatment	Involvement subscale from the Immersive Tendency Questionnaire (ITQ – Involvement subscale) [54]	7
	Acceptability	System Usability Scale (SUS) [53]	10
	Perceived treatment assignment	Perceived Treatment Assignment survey	1

^a^DVPRS: Defense and Veterans Pain Rating Scale.

^b^PROMIS: Physical Function and Sleep Disturbance.

^c^VR: virtual reality.

^d^The 4 questions were selected from the PCS to decrease participant burden.

^e^cLBP: chronic lower back pain.

**Table 2 table2:** Timeline of measures.

Measure	Pre-treatment (days –14 to 0)		Active treatment (days 1-56)		Postintervention (months 1-6 after the end of the study)			
	Baseline assessment (Day –14)	Pain surveys (Days –10, –7, –4, and 0)	Biweekly surveys	End of treatment (day 56)	Follow up 1 month	Follow up 2 months	Follow up 3 months	Follow up 6 months
DVPRS-I^a^ and DVPRS-II	X	X	X	X	X	X	X	X
PGIC^b^				X	X	X	X	X
PROMIS^c^ physical function	X			X	X	X	X	X
PROMIS sleep disturbance	X			X	X	X	X	X
Pain self-efficacy measures	X			X	X	X	X	X
PCS^d^	X			X	X	X	X	X
CPAQ-8^e^	X			X	X	X	X	X
Opioid use	X			X	X	X	X	X
Health care utilization	X			X				
Patient satisfaction					X	X	X	X
Device utilization			X	X				
VR^f^ usage data			X	X				
PANAS^g^	X			X				
SUS^h^				X				
ITQ^i^—involvement subscale	X							
Perceived treatment assignment								X

^a^DVPRS: Defense and Veterans Pain Rating Scale.

^b^PGIC: Patient’s Global Impression of Change.

^c^PROMIS: Physical Function and Sleep Disturbance.

^d^PCS: Pain Catastrophizing Scale.

^e^CPAQ-8: Chronic Pain Acceptance Questionnaire.

^f^VR: virtual reality.

^g^PANAS: Positive and Negative Affect Schedule.

^h^SUS: System Usability Scale.

^i^ITQ: Immersive Tendencies Questionnaire.

### Data Collection, Quality Control, and Confidentiality

All questionnaires will be completed by participants electronically via the REDCap Cloud platform. We will collect information at every stage of recruitment, randomization, and treatment in accordance with the CONSORT (Consolidated Standards of Reporting Trials) guidelines [57]. The Western Institutional Review Board approved this study. Given the safety of the device seen in past studies [7,31], Western Institutional Review Board did not deem that this study would require Data Safety and Monitoring Board oversight.

### Compensation

Participants will receive a total of US $150 (US $6 per completed survey) for their participation in the entire study. Two payments will be processed. The first payment will be distributed at the end of the 8-week program (US $126 possible; prorated) and upon return of their VR headset (prepaid shipping will be provided). The second payment will be distributed after the last follow-up survey (US $24 possible; prorated). All payments will be in the form of an Amazon eGift Card.

In addition to their monetary compensation, all participants will be eligible to receive a gift VR headset 6 months after their completion of treatment if they complete 16 or more of the 21 surveys administered during the active treatment phase, confirm their interest in receiving a VR headset, and return their VR treatment study headset.

### Safety Monitoring

Participants were provided with contact information and encouraged to contact as needed. Safety will be monitored by following up with participants for any adverse events they communicate to the support staff. Additionally, adverse experiences with using VR will be assessed using the question, “Did you experience any motion sickness or nausea while using VR?” on 4-point with 0 (Never), 1 (Sometimes), 2 (Often), and 3 (Always). Similar to prior work, VR side effects will be assessed at the end of treatment [32].

### Sample Size Determination

In terms of sample size considerations, a power analysis was performed using data from a recent at-home cLBP study that we conducted. DVPRS pain intensity scores were collected from 39 individuals at baseline, during, and immediately following a 21-day, skills-based VR intervention, and from 35 individuals at baseline, during, and immediately following an audio-only version of the 21-day program. The average difference score was 1.48 for the VR group and was 0.756 for the audio-only group (on an 11-point scale). Assuming an α level of .05 and 90% power, we would need 45 participants per group to observe a treatment × time interaction. In case of high attrition (40%), we will randomize at least 75 participants per group and if possible up to 90 participants per group.

### Statistical Analyses

#### General Approach

Checks of assumptions underlying statistical procedures will be performed and all corrective procedures will be applied as necessary. All analyses will involve 2-sided hypothesis tests, with α=.05 and adjusted for any multiple comparisons within the family of tests as appropriate.

Group equivalence will be assessed through univariate tests of association between treatment groups (EaseVRx/Sham VR) for all baseline demographic and clinical variables with chi-square and Kruskal–Wallis tests applied as appropriate. If statistically significant differences between groups are found for any variables (*P*<.05), those will be controlled for in the mixed models.

The data will be analyzed in a mixed-model framework (PROC GLIMMIX in SAS) with 3 explanatory factors: treatment group, time, and time × treatment group. Treatment group, EaseVRx versus Sham VR, will be specified as a between-subjects factor. Time will be specified as a within-subjects factor. The effect of interest will be the time × treatment group effect which tests whether the treatment group influenced the trajectory of the key variables over time.

The analytic method used will not involve imputing missing data for estimating the significance of the effects specified in the model. However, the predicted values from the estimated model will be used for reporting the findings. Given the safety of this treatment, there is no plan to conduct interim analyses.

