#### Primary Analyses

The primary endpoint will be the time course of DVPRS-I Pain scale rating at baseline (defined as the average of 3 DVPRS-I Pain Scale ratings obtained during the 2 weeks before enrollment/randomization), at 8 weekly time points (twice per week) across the 8-week intervention, and immediately following the intervention. We will use a linear mixed model as described above.

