#### Secondary Analyses

Several analyses will be proposed.

First, we will compare the PGIC scale at end of treatment and follow-ups.

Second, we will repeat similar analyses as above for 2 time points, baseline and immediately following the 8-week intervention for opioid drug use, PROMIS physical function, PROMIS sleep disturbance, PSEQ-2, PCS, and CPAQ-8.

Finally, we will repeat similar analyses as above for 2 time points, the day immediately following the 8-week intervention and 1 month after the intervention for DVPRS Pain Rating, opioid drug use, PROMIS physical function, PROMIS sleep disturbance, PSEQ-2, PCS, and CPAQ-8.

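### Covariates are chosen by baseline significance tests that neither fix the model in advance nor control the effect being tested, and baseline is left as an unconstrained response level, which costs precision mainly in the secondary outcomes

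*Protocol article*

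**What the plan says.** All references are to the Statistical Analyses section of the protocol article.

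- **Screening (General Approach).** The arms are compared "for all baseline demographic and clinical variables with chi-square and Kruskal–Wallis tests applied as appropriate".
- **Consequence (General Approach).** "If statistically significant differences between groups are found for any variables" at P<.05, "those will be controlled for in the mixed models". No covariate is named in advance.
- **Model (General Approach).** A mixed model "with 3 explanatory factors: treatment group, time, and time × treatment group". The target is fixed: "The effect of interest will be the time × treatment group effect".
- **Baseline in the primary analysis (Primary Analyses).** Baseline, a mean of three ratings, is one of the response time points: "The primary endpoint will be the time course of DVPRS-I Pain scale rating at baseline". Nothing says that the arms share a baseline mean.
- **Baseline in the secondary analyses (Secondary Analyses).** The same model is applied to "2 time points, baseline and immediately following the 8-week intervention for opioid drug use". The other outcomes treated in this way are CPAQ-8, PCS, PSEQ-2 and the two PROMIS scales (physical function and sleep disturbance). A further set compares end of treatment with 1 month, and there the pretreatment value does not appear.

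**The concern.** Allocation is randomised 1:1, so a significant baseline difference reflects chance and says nothing about whether the variable predicts pain. A rule driven by such tests picks covariates by imbalance instead of prognosis, and the fitted model cannot be written down until the data are seen.

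The rule also fits badly with the model it feeds. The target is an interaction with time, which a baseline main effect hardly touches. Baseline DVPRS-I is itself a baseline clinical variable, so if it met the P<.05 rule it would be a covariate and a response in the same model.

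The second strand is efficiency. With baseline as a free response level, group × time over two time points is a comparison of raw change scores. That is valid, but less precise than conditioning on a baseline that is already collected.

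**Working it through.** The plan gives no figure of its own for this point. Its sample size (45 per group, raised to 45/(1−0.40) = 75 for attrition) is not in question here and is not used below.

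**1. How often the rule fires.** The Demographics section lists 11 variables. Table 2 marks 10 measures at the baseline assessment: DVPRS, PROMIS physical function, PROMIS sleep disturbance, pain self-efficacy, PCS, CPAQ-8, opioid use, health care utilization, PANAS and ITQ. That makes 21, or somewhat more if measures are split into parts; 20 to 25 is a fair range. For k independent tests at .05, P(at least one) = 1 − 0.95^k and the expected number is 0.05k.

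| k | P(at least one enters) | Expected number |
|---|---|---|
| 20 | 64% | 1.0 |
| 25 | 72% | 1.25 |

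**2. What an entered covariate does to the target.** For participant i with covariate x entered as a main effect:

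- Y(i,0) = a + b·x + c·group + e(i,0)
- Y(i,1) = a + t + b·x + c·group + d·group + e(i,1)
- Difference: Y(i,1) − Y(i,0) = t + d·group + error

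The term b·x cancels. With complete data, d is estimated from the differences alone, so adding x changes nothing. A simulated complete two-time-point data set with an imbalanced prognostic covariate gave −0.6946 (SE 0.2103) with and without the covariate. In a second simulation (random intercept, 75 per arm, 30% of post-treatment values missing), adding the covariate moved the estimate by 0.02 on average, against an SE of about 0.18, and the SE ratio was 0.99.

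**3. Type I error.** A separate simulation applied test-then-adjust to a single outcome, not to the interaction, with 45 per arm. With one covariate correlated 0.6 with the outcome, the error rate was 4.1% against a nominal 5%. With ten weak covariates it was 4.6%. Neither shows inflation.

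**4. Precision with a single baseline reading (secondary outcomes).** Take equal variance s² at both times and correlation ρ.

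- Change score: 2s²(1 − ρ)
- Adjusted for baseline: s²(1 − ρ²)
- Ratio: (1 + ρ)/2

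**5. Precision for DVPRS-I.** Take a baseline that is the mean of three ratings, one post-treatment rating, and the same correlation ρ between all ratings. The variance of the baseline mean, in units of s², is v = (1 + 2ρ)/3. The ratio is (1 − ρ²/v)/(1 + v − 2ρ). At ρ = 0.5, v = 0.667 and the ratio is 0.625/0.667 = 0.94.

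| Assumed ρ | Ratio, single baseline | Ratio, three-rating baseline |
|---|---|---|
| 0.3 | 0.65 | 0.89 |
| 0.5 | 0.75 | 0.94 |
| 0.7 | 0.85 | 0.97 |
| 0.8 | 0.90 | 0.98 |

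The variance saved is therefore 10% to 35% for the secondary outcomes and about 2% to 11% for DVPRS-I. The article gives no correlation, so every ρ here is an assumption.

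**The case against.** The strongest reply is that little harm follows. The covariate rule barely reaches the interaction being tested, type I error holds, and an unconstrained repeated-measures model is unbiased under randomisation. Baseline is used, as a response level, and the model matches the treatment × time basis of the sample size. Whether baseline means are constrained might be called a detail for the analysis plan.

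Most of this stands, and it limits the point. It does not remove it. The P<.05 rule is stated, so an analysis plan would have to reverse it, not fill it in. That the rule hardly affects the target is a reason to drop it, since it makes the model unpredictable in return for almost no control. Conditioning on baseline improves a stated method at no cost in data.

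Three stronger readings are tempting and are not supported:

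- **That the rule produces false positives, or biases the primary result.** Steps 2 and 3 show neither.
- **That power would rise from 90% to 98%, 96% or 94% (ρ = 0.3, 0.5, 0.7).** Those figures pair the effect size behind the DVPRS-I sample size with a single-reading baseline. DVPRS-I has a three-rating baseline, and the secondary outcomes have no stated effect size or power.
- **That the chance of at least one covariate entering is nearer 79%.** That needs about 30 independent tests (1 − 0.95^30). It is reached only by splitting measures into items and counting state and zip code, although zip code is collected to derive a rural or urban class. Related pain measures are also not independent, so even 64% to 72% is a guide.

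**Conclusion.** The point holds in two parts.

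First, the P<.05 rule should go. It makes the model depend on chance imbalance, with a probability of about 64% to 72% that at least one covariate enters (20 to 25 independent tests). It does not deliver its intended control of the group × time effect, and it allows the outcome's own baseline to sit on both sides of the model. The harm is an unpredictable model, not false positives.

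Second, the six two-time-point secondary outcomes lose precision that could be recovered: variance would fall to 0.65–0.90 of its present value for assumed ρ of 0.3–0.8. For the primary outcome the gain is small, about 2% to 11% under the assumed common correlation and one post-treatment rating. These ratios rest on equal variances and a linear relation with baseline; for a measure that may be skewed, such as opioid dose, they are only a guide. The change is worth making, but the validity of the trial does not depend on it.

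**What to change.** 1. Delete the baseline significance tests and the P<.05 inclusion rule. Tabulate baseline characteristics by arm without P values.
2. Name any further covariates, chosen for prognosis, before unblinding.
3. For outcomes with a pretreatment value, keep baseline in the response and constrain its mean to be equal across arms. Group × time then remains the target.
4. If baseline is instead made a covariate with post-baseline responses only, restate the target as the group difference at named time points. Group × time over post-baseline visits alone would miss a constant treatment difference.
5. In the end-of-treatment versus 1-month models, the constraint can be used only if the pretreatment value is added as a response level. It must not be placed on the end-of-treatment means, which follow randomisation.
6. Exempt PGIC, which has no baseline in Table 2.

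No new data are needed; the baseline values are already collected. The cost is a dated change to the protocol and analysis plan. Because the article reports recruitment complete and a primary manuscript in preparation for submission, the change should be recorded as late and as made before unblinding.

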#### Primary Analyses

The primary endpoint will be the time course of DVPRS-I Pain scale rating at baseline (defined as the average of 3 DVPRS-I Pain Scale ratings obtained during the 2 weeks before enrollment/randomization), at 8 weekly time points (twice per week) across the 8-week intervention, and immediately following the intervention. We will use a linear mixed model as described above.

#### Secondary Analyses

Several analyses will be proposed.

First, we will compare the PGIC scale at end of treatment and follow-ups.

Second, we will repeat similar analyses as above for 2 time points, baseline and immediately following the 8-week intervention for opioid drug use, PROMIS physical function, PROMIS sleep disturbance, PSEQ-2, PCS, and CPAQ-8.

Finally, we will repeat similar analyses as above for 2 time points, the day immediately following the 8-week intervention and 1 month after the intervention for DVPRS Pain Rating, opioid drug use, PROMIS physical function, PROMIS sleep disturbance, PSEQ-2, PCS, and CPAQ-8.

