### Technical Support

Participants will be provided with onboarding material as well as emails describing the study procedures and details. Instructional videos will be made available to participants, and access to remote technical support will be provided. VR usage data for both treatment groups will be surveyed twice a week for the intervention’s 8-week duration.

Survey data will be monitored for completion and technical support staff will be available. Participants will receive a telephone number and email address to contact support staff as needed. The technical support staff will also reach out if there is low adherence to the devices, lack of survey data, or low battery power detected on the headset’s remote monitoring dashboard. Twice weekly, the research staff will review the REDCap Cloud survey dashboard to assess if participants are completing the study. If a survey is missed, the REDCap Cloud system will send up to 2 reminders 24 hours apart. If the participant does not respond to the reminders, a research staff member will send an email or SMS text message to understand why there has been no response and encourage them to re-engage with the study. If the survey remains incomplete after 2 weeks of no data, the participant will be deemed lost to follow up. The participant could come back to the study at any time.

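### Six secondary outcomes are analysed in separate two-visit models, which leave the later scores of returners out of the end-of-treatment contrast and the baseline out of the one-month contrast; one joint model is a modest, cheap improvement

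*Protocol article*

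**What the plan says.** The General Approach section sets a mixed model with arm, time and arm × time, and time as a within-subjects factor. On missing data it states: "The analytic method used will not involve imputing missing data for estimating the significance of the effects specified in the model".

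The Secondary Analyses section applies this framework to pairs of visits:

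- **First pair.** "we will repeat similar analyses as above for 2 time points, baseline and immediately following the 8-week intervention for opioid drug use", together with PROMIS physical function, PROMIS sleep disturbance, PSEQ-2, PCS and CPAQ-8.
- **Second pair.** The same six outcomes plus the DVPRS pain rating, at "2 time points, the day immediately following the 8-week intervention and 1 month after the intervention".
- **PGIC** is handled separately, at end of treatment and the follow-ups.

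Table 2 schedules all six outcomes at baseline, day 56 and months 1, 2, 3 and 6. The Overview requires a baseline assessment before the treatment phase. On participants who stop responding, the Technical Support section says: "The participant could come back to the study at any time". Sample Size Determination allows for 40% attrition as a contingency.

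**The concern.** A likelihood-based mixed model without imputation handles missing data only through the observations it is given. Restricting it to two visits has two consequences.

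1. In the baseline/day-56 model, a person who misses day 56 but answers at month 1 or later contributes the baseline only. The later scores, which would help to predict the missing one, are left out. Missingness at day 56 must then be explained by arm and baseline alone.
2. In the day-56/month-1 model, the baseline is not among the visits. Someone absent at both of those visits contributes nothing, although a baseline exists. Missingness related to the outcome's baseline level is not accounted for unless that baseline happens to enter as a covariate.

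At stake are the precision and, under some mechanisms, the bias of the end-of-treatment and one-month results for these outcomes.

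**Working it through.** **The plan's own figures.** The plan gives no figure for this choice. The nearest is the sample size: "Assuming an α level of .05 and 90% power, we would need 45 participants per group to observe a treatment × time interaction". The attrition step reproduces: 45/(1 − 0.40) = 75. The 45 itself cannot be checked, because no SD or correlation is given. Nothing below depends on it.

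**Inputs.** From the protocol article: up to 90 per arm, 1:1 allocation, baseline required, time as a factor, no imputation. Assumed, because the article does not give them:

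- SD 1 at every visit.
- Correlation ρ of baseline with later visits, 0.5-0.6.
- Correlation τ among post-treatment visits, 0.6-0.8, equal for all pairs.
- Fraction missing day 56, 10-40%; 30-70% of these return and then complete the follow-ups. Everyone seen at day 56 also completes the follow-ups.

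Let n be the number per arm, r the fraction seen at day 56, and q the fraction seen later, so q = r + (1 − r) × return rate. Let π = (τ − ρ²)/(1 − ρ²), the partial correlation of two post-treatment visits given baseline.

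**Variance of the arm difference in change from baseline to day 56**

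- Completers only: (2/n) × 2(1 − ρ)/r
- Two-visit mixed model: (2/n) × [(1 − ρ²)/r + (1 − ρ)²]
- Joint model: (2/n) × [(1 − ρ²){(1 − R²)/r + R²/q} + (1 − ρ)²], where R² = π² with month 1 only and R² = 4π²/(1 + 3π) with all four follow-ups

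**Worked example:** n = 90, ρ = 0.5, τ = 0.7, 40% missing, half returning. Then r = 0.6, q = 0.8, π = 0.45/0.75 = 0.6.

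| Model | Bracket | SE |
|---|---|---|
| Completers only | 2(0.5)/0.6 = 1.667 | 0.192 |
| Two visits | 0.75/0.6 + 0.25 = 1.500 | 0.183 |
| Three visits (R² = 0.36) | 0.75(0.64/0.6 + 0.36/0.8) + 0.25 = 1.3875 | 0.176 |
| Six visits (R² = 1.44/2.8 = 0.514) | 0.75(0.486/0.6 + 0.514/0.8) + 0.25 = 1.339 | 0.173 |

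The variance ratio to the two-visit model is 1.3875/1.5 = 0.925 with three visits and 1.339/1.5 = 0.893 with six. The two-visit model is already at 1.5/1.667 = 0.90 of completers only, because the baselines of people who miss day 56 are kept.

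**Ends of the range**

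- Smallest gain (ρ = τ = 0.6, 10% missing, 30% returning; r = 0.9, q = 0.93, π = 0.375). Two visits: 0.64/0.9 + 0.16 = 0.8711. Three visits (R² = 0.1406): 0.8679, ratio 0.996. Six visits (R² = 0.2647): 0.8650, ratio 0.993.
- Largest gain (ρ = 0.5, τ = 0.8, 40% missing, 70% returning; r = 0.6, q = 0.88, π = 0.733). Two visits: 1.500. Three visits (R² = 0.538): 1.286, ratio 0.857. Six visits (R² = 0.672): 1.233, ratio 0.822.
- Nobody returns: q = r, the braces reduce to 1/r, and the ratio is exactly 1.

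**Day 56 to month 1, same worked example.** The two-visit model has bracket (1 − τ²)/r + (1 − τ)²/q = 0.51/0.6 + 0.09/0.8 = 0.9625. Adding the baseline gives (1 − ρ²)[(1 − π²)/r + (1 − π)²/q] = 0.75(0.64/0.6 + 0.16/0.8) = 0.950. The ratio is 0.987, a gain of about 1%.

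**Bias of the day-56 contrast** (large-sample maximum likelihood, 200,000 per arm, true contrast −0.40 SD, about 20-28% missing, ρ = 0.5, τ = 0.5 or 0.7)

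| Missing day 56 depends on | Two visits | All visits |
|---|---|---|
| Nothing, or baseline only | about 0 | about 0 |
| Month-1 score, all return | −0.03 to −0.05 | about 0 |
| Unseen day-56 score, about half return | −0.07 to −0.08 | −0.04 to −0.08 |

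**The case against.** The strongest reply is that a two-visit mixed model is a valid analysis, and that fixing end-of-treatment results on end-of-treatment data is a legitimate choice. Most of its supporting points stand.

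- **Returners are an assumption.** The article gives no return rate, and the Technical Support sentence is a permission, not a forecast. The 40% is a contingency, and permanent dropout is the pattern in which the joint model gains nothing. This stands, and is why the size is given as a range that falls to zero when nobody returns.
- **A multi-visit analysis is planned.** The third exploratory analysis takes the same outcomes through months 1, 2, 3 and 6. It does not settle the point: it is exploratory and, although the section opens with mixed models, it is named a 2-factor ANOVA. In its classical form that would drop anyone with a missed visit.
- **Baseline could still enter the second model.** General Approach adjusts for baseline variables that differ significantly between arms. That covers an outcome's baseline only if it happens to pass that test.
- **Timing.** The primary manuscript was planned for winter 2020, with data collection open until March 2021. This weighs against a six-visit model, which would also bring the exploratory six-month visit into a secondary estimate. It does not weigh against a three-visit model, since Secondary Analyses already needs month 1.
- **The day-56-to-month-1 contrast is a question of its own**, about durability. Replacing it with change from baseline would alter the estimand, so it has to be kept.

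A reader might go further and infer that someone who misses day 56 adds nothing to the end-of-treatment effect. The documents do not support that: the model is mixed and the baseline is mandatory, so such a person's baseline is used. Across the settings examined this already lowers the variance by 2-10% against completers only.

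**Conclusion.** The point holds as a modest inefficiency in the secondary analyses of six outcomes. It is not an error that invalidates them. Under the assumed correlations, with 10-40% missing day 56 and 30-70% of those returning, a joint model lowers the variance of the day-56 contrast by about 0.4-14% with three visits and 1-18% with six. It never raised the variance in the settings examined. These figures require time as a factor, an adequate covariance structure and roughly normal scores, so they do not carry over directly to opioid use.

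Two broader readings are not supported. A joint model does not reduce bias in general: there is no difference when missingness is random or depends on baseline, the bias is removed when missingness depends on later scores that are observed, and the reduction is partial to negligible when it depends on the unseen day-56 score. Nor does the point cover every efficacy result: PGIC is not fitted in this way, and the primary DVPRS-I analysis already uses all on-treatment assessments.

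**What to change.** For each of the six outcomes, replace the two pairwise models with one mixed model over at least baseline, day 56 and month 1, with categorical time, arm × time and an unstructured covariance. For opioid use, choose a model suited to its distribution. From that model report:

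1. the arm difference in change from baseline to day 56;
2. the planned arm difference in change from day 56 to month 1;
3. optionally, the arm difference in change from baseline to month 1.

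If wanted, state in advance that the model will be refitted with months 2, 3 and 6 when follow-up closes, and which fit is the reported secondary result.

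The cost is a change of analysis wording. The three-visit model needs no data beyond what Secondary Analyses already uses. The small downside of a six-visit refit is that it is final only after follow-up closes.
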